#### Study Plan

##### Integration of HIRAID® Inpatient framework into hospital systems

The local electronic and paper-based documentation systems will integrate the HIRAID® Inpatient documentation templates. HIRAID® Inpatient will include a standardised template with fields and prompts for all framework elements. Hospital local factors, such as paper or electronic documentation will inform adaptation practices. Features like the product(s) used (e.g. PowerChart, Cerner electronic medical records (eMR)), automation features, and compatibility with existing tools are included. The documentation templates are designed to streamline assessment documentation, minimise duplication, alleviate administrative burdens, and reduce redundancies for hospital ward nurses. The HIRAID® Inpatient framework will be implemented alongside existing standard nursing care. No concurrent interventions are prohibited during the implementation period; however, any new initiatives or changes to routine care that may influence study outcomes will be documented.

##### Education and training of nursing staff

All nursing staff will participate in education sessions designed to teach the theory and application of HIRAID® Inpatient, using a pedagogically informed approach [32]. The education programme will be co-developed with experts from the participating organisations and will incorporate principles of constructive alignment [33–35], backwards design [36] and scaffolded learning [37] to ensure coherence between learning outcomes, resources and activities.

The education programme will consist of two different training sessions, the instructor and the provider training. The HIRAID® Inpatient Instructor training will be designed to equip healthcare professionals with the skills to teach and implement the framework, and focuses on developing teaching strategies, and applying HIRAID® to a clinical setting. CNCs/CNEs and senior nurses at each site will receive HIRAID® Inpatient Instructor training and will lead delivery of HIRAID® Inpatient Provider courses for all RNs and ENs from participating wards using a train-the-trainer model. Senior RNs will undergo Instructor training to independently deliver HIRAID® Inpatient training, supporting long-term sustainability. The HIRAID® Provider training will focus on equipping clinicians with the skills to use the framework. Completion of the HIRAID® Inpatient Provider Course will be mandatory for new nursing staff and will be embedded into orientation and onboarding programmes through the established instructor network.

##### Supporting materials

Multiple strategies, developed during Phase 2, will be implemented to address hospital-specific barriers and support the rollout. Co-designed educational resources will ensure accessible learning and ongoing support. Environmental prompts, such as posters and reference cards, will serve as quick reminders of the HIRAID® Inpatient framework and its components. Implementation research nurses, along with nurse champions from the workforce, will play a key role in encouraging adoption. These nurses will perform fortnightly audits of nursing documentation to track progress, document the implementation strategies used within their assigned cluster, provide updates, identify teaching opportunities, and address any challenges that arise during implementation. See Figs. 4 and 5 for the overall process of HIRAID® Inpatient implementation and outcome measurement (Phase 3).

**Fig. 4 Fig4:**
[figure not shown]
The overall process for the implementation and outcome measurement of the HIRAID® Inpatient intervention

**Fig. 5 Fig5:**
[figure not shown]
The schedule of enrolment, intervention, and assessments for HIRAID® Inpatient: Implementation evaluation of an evidence-informed hospital inpatient nursing framework (adapted from [59])

#### Outcomes

##### Patients with a preventable clinical deterioration (H_1_)

Rate per 1000 admissions of preventable patient deterioration calls (RRT calls) related to nursing assessment and management, observation and monitoring. RRT activation is already recorded in local databases and will be used to identify patients for medical record review, independent assessment and verification of causal factors [38]. Secondary outcome is transfer to a higher level of care (e.g. to Intensive Care Unit) (Table 3).

**Table 3 Tab3:** Summary of HIRAID® Inpatient outcome measure, data collection sources and measurement timepoints

Outcome	Outcome description	Outcome measure	Data analysis	Data source	Control (pre)	Implementation	Intervention (post)
Patient health outcomes							
Outcome 1 (H1)	Nursing-related preventable clinical deterioration	Incidence of clinical deterioration events related to nursing assessment and care	*Descriptive approach, generalised linear model (GLM) approach	Patient deterioration database, eMR records	✓	-	✓
Outcome 2 (H1)	Transfer to higher level care	Incidence of patients transferred to higher level care	*Descriptive approach, GLM approach	Patient deterioration database, eMR records	✓	-	✓
Outcome 3 (H2)	Hospital Acquired Complications (HACs) influenced by nursing care	Incidence of patient days with respiratory complication (HAC03), and/or healthcare-associated infections (HAC06)	*Descriptive approach, GLM approach	Health District data collections, Performance Planning Unit (PPU) database, eMR records	✓	-	✓
Outcome 4 (H2)	HACs influenced by nursing care–health service perspective	Incidence of hospital resource use and costs	*Descriptive approach, GLM approach	Health District data collections, PPU database, eMR records	✓	-	✓
Outcome 5 (H2)	HACs influenced by nursing care	Rate of all other HACs (not HAC03 and HAC06)	*Descriptive approach, GLM approach	Health District data collections, PPU database, eMR records	✓	-	✓
Outcome 6 (H3)	Events that cause patient harm or near miss	Incidence/proportion of adverse patient harm or near miss events	*Descriptive approach, GLM approach	Health District data collections, PPU database, eMR records	✓	-	✓
Patient and carer experience outcomes							
Outcome 7 (H4)	Patient and carer perceptions and experience of nursing care	Average score reported on the Australian Hospital Patient experience question set and Schmidt's Perceptions of Nursing Care Survey	*Descriptive approach, logistic regression for binary outcome variables, linear regression for continuous outcome variables	eMR records, patient/carer satisfaction surveys, patient complaints	✓	-	✓
Outcome 8 (H4)	Patient and carer overall care experience and patient complaints relating to nursing care	Average scare reported on remainder Schmidt’s Perceptions of Nursing Care Survey, and content analysis of complaints	*Descriptive approach, logistic regression for binary outcome variables, linear regression for continuous outcome variables	eMR records, patient/carer satisfaction surveys, Patient complaints	✓	-	✓
Staff experience and capability outcomes							
Outcome 9 (H5)	Staff satisfaction with communication (handover)	Average score on Staff Satisfaction with Handover Surveys (Inter-professional communication)	*Descriptive approach, multiple linear regression modelling, logistic regression for binary outcome variables, linear regression for continuous outcome variables	Nursing/allied health/medical staff surveys	✓	-	✓
Outcome 10 (H5)	Nurse confidence in patient assessment and escalation of care	Average score on Confidence with communication survey	*Descriptive approach, multiple linear regression modelling	Nursing/allied health/medical staff surveys	✓	-	✓
Outcome 11 (H5)	Quality and quantity of nursing documentation	Average score of modified D-catch tool	*Descriptive approach, multiple linear regression modelling	Nursing/allied health/medical staff surveys	✓	-	✓
System-level and Implementation outcomes							
Outcome 12 (H6)	Acute treatment costs	Average of incremental net health service cost per rapid response team calls avoided	*Descriptive approach, Extrapolation modelling, time horizon modelling, Discrete event simulation (stochastic)	Health District data collections, PPU(Costs) database	✓	-	✓
Outcome 13 (H7)	Implementation fidelity	Outcomes reported on the implementation fidelity surveys and nurse interviews	*Descriptive approach, process evaluation, structured fidelity scoring	Audits, Nursing staff interviews, Nurse facilitator survey	-	✓	✓

*Descriptive approach—means and standard deviation for continuous variables, and frequencies and percentages for categorical variables. Cluster comparisons—ANOVA for continuous variables; Pearson’s Chi-Square tests for categorical variables

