### Phase 3: Implementation evaluation of HIRAID® Inpatient

#### Study design

In Phase 3, the HIRAID® Inpatient framework will be implemented using a Type II effectiveness-implementation hybrid design [29], including a SW-cRCT [30]. The hybrid approach allows testing of the implementation strategy at the same time as observing the outcomes of the intervention [29, 30]. Four clusters will be progressed through three sequential phases: control, intervention transition and post-intervention, with a staggered rollout and a 1:1 allocation ratio, with most data collected from each defined population as outlined in Table 4. The trial is structured within a superiority framework, aiming to demonstrate improved outcomes compared to usual care.

Each participating hospital ward (cluster) will begin in the control phase, representing a period of routine or usual care before the scheduled implementation of the HIRAID® Inpatient framework. During this phase, baseline data and behavioural diagnostics will be collected to serve as the comparator for the intervention. Rather than using a separate, concurrent control group, this SW-cRCT uses each cluster as its own control. Data gathered during the pre-intervention phase will be directly compared with data collected post-implementation. This design enables evaluation of the intervention against established, real-world clinical practice. The HIRAID® Inpatient intervention will then be implemented over a three-month period (Intervention Transition), followed by an intervention data collection period, lasting between 3 and 12 months, depending on the cluster (Fig. 3).

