#### Study setting

To ensure geographically and clinically diverse settings, the study will take place in three local health districts in two states, comprising a total of 10 hospitals and 35 wards (total 834 beds) from Illawarra Shoalhaven and Western Sydney Local Health Districts in New South Wales, and Eastern Health in Victoria. The ten hospitals will be nested into one of four clusters based on geography and clinical governance to mitigate the risk of contamination. Collectively the study wards manage 4050 patient admissions per month and employ 1259 nurses (Table 2). These hospitals were selected as they admit acutely unwell patients directly from the ED—the patients most at risk for adverse events [4].

**Table 2 Tab2:** Profiles of the ten participating hospitals, including description, hospital acquired infections (per 1000), the annual number of admissions, and ward type

Cluster	Health Service data for 2023		Study ward data for 2023	
	Description	HAI:1000	Admits per year	Ward type
1. Illawarra Shoalhaven North, NSW (Wollongong hospital—6 wards)	Regional: 684 km^2^, Pop: 214,000 +	3.22	11,400	Aged Care, Gastroenterology, General Medicine, Renal, Respiratory, Surgical
2. Illawarra Shoalhaven South, NSW (Shellharbour Hospital—4 wards; Shoalhaven Hospital—4 wards; Milton/Ulladulla Hospital—1 ward)	Rural Regional: 4708 km^2^, Pop: 185,000 +	2.34	12,861	Aged Care, General Medicine, Surgical
3. Western Sydney, NSW (Westmead Hospital—5 wards; Blacktown/Mount Druitt Hospital—7 wards; Auburn Hospital—1 ward)	Metro: 780 km^2^, Pop: 946,000 +	2.35	13,367	Aged Care, Orthopaedics, Cardiology, General Medicine, Haematology, Neurosurgery, Renal, Respiratory, Stroke
4. Eastern Health, VIC (Box Hill Hospital—4 wards; Angliss Hospital—2 wards; Maroondah Hospital—2 wards)	Metro: 2816 km^2^, Pop: 750,000 +	3.33	10,981	General Medicine, Speciality Medicine, Stroke, Surgical (general, plastic surgery and gastric surgery)
10 hospitals	Pop: 2.1 million +		48,609	

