#### Randomisation

Each cluster will be randomly allocated to one of four starting dates for implementation. Randomisation will be performed by the study statistician using computer-generated numbers. Participating wards will have no influence over the allocation prior to randomisation, ensuring concealment of the allocation sequence until wards are assigned. No further changes to clusters will be made once the allocation has been finalised to minimise the risk of bias.

We are unable to randomise sites to clusters because of geographical location and clinical governance. The significant geographical distance between sites, mitigates the risk of contamination due to reduced proximity. Randomising clusters based on health service provides consistent clinical governance for study operations.

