#### Sample size

Sample sizes were calculated for each of the hypotheses. Hypotheses H1, H2, H3, and H6 sample size estimations were conducted collectively, as they will use medical record and cost data from relevant systems for the period of 1 st July 2026 to 1 st December 2027 (Table 4—shaded grey). To maximise the study’s power in detecting true differences, should they exist, the largest sample size estimation is reported and will be used. Sample sizes were calculated with an assumed intra-class correlation of 3%, 5% significance (two-tailed) and 80% power, and applying Woertman’s SW design estimate approach [48]. These sample sizes have been calculated using the most recent data from the study sites and/or previous work by the investigators in this field. To evaluate implementation fidelity HIRAID® facilitators (CNCs/CNEs) employed to assist with education and roll out will be invited to participate in the evaluation of implementation fidelity. The number of staff to be involved in this process will be determined by each LHD.

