#### Statistical methods

##### HIRAID® effectiveness/clinical outcomes

Survey and health record data collected for implementation evaluation will be analysed using descriptive statistics to assess fidelity levels and feedback from study sites. Descriptive statistics will be calculated using the chi-square test for categorical variables, and the *T*-test (normally distributed data) or the Mann-Whitney *U* test (non-normally distributed data) for continuous variables. All analyses will follow the intention-to-treat principle, with all clusters evaluated according to their original group allocation, regardless of adherence or protocol deviations. Comparisons within and across clusters will be conducted using the generalised linear mixed model (GLMM) approach, applying appropriate link functions tailored to each outcome variable. For binary outcome measures, a GLMM with a binary logistic link function will be used, while for count outcome measures, GLMMs with Poisson or negative binomial link functions will be applied. The model will account for the random effect of the cluster and will adjust for relevant confounders, identified in the descriptive analyses, as fixed effects. SPSS V28™ (IBM Corp., Armonk, NY, USA) will be used and the alpha set to < 0.05 [18].

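### Table 3 lists unclustered regressions, in conflict with the mixed model in Statistical methods and the 3% ICC, and the design text calls a ward a cluster although four hospital groups are randomised

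*Protocol article*

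**What the plan says.** All references are to the protocol article.

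- **Table 3, Outcomes 1 to 6 (H1 to H3).** The analysis is given as a "generalised linear model (GLM) approach", abbreviated to GLM after the first row.
- **Table 3, Outcomes 7 to 11 (H4 and H5).** Outcomes 7, 8 and 9 carry "logistic regression for binary outcome variables, linear regression for continuous outcome variables". Outcome 9 also lists multiple linear regression, and Outcomes 10 and 11 list only that. Most of these measures are average scores.
- **Statistical methods, HIRAID® effectiveness/clinical outcomes.** "Comparisons within and across clusters will be conducted using the generalised linear mixed model (GLMM) approach", with link functions chosen to suit each outcome and a random effect for the cluster. Specific models follow for binary outcomes (logistic) and count outcomes (Poisson or negative binomial). Continuous outcomes get no sentence of their own.
- **Sample size.** "Sample sizes were calculated with an assumed intra-class correlation of 3%, 5% significance (two-tailed) and 80% power", using Woertman's "SW design estimate approach".
- **What a cluster is.** Study setting: "The ten hospitals will be nested into one of four clusters". Randomisation: "Each cluster will be randomly allocated to one of four starting dates for implementation". The Phase 3 Study design section first speaks of four clusters, then says in its next paragraph: "Each participating hospital ward (cluster) will begin in the control phase".

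**The concern.** The article gives two analysis rules for the same outcomes. GLM in Table 3 may be a loose abbreviation for GLMM, but multiple linear regression cannot be read as a mixed model. The conflict is therefore clearest for H4 and H5. For their continuous scores, Table 3 is the only place that names a model.

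In a stepped wedge the clusters contribute unequally to the two conditions: an early cluster supplies mostly intervention data and a late one mostly control data. Differences between clusters then leak into the treatment contrast, and an ordinary regression does not count that variance. Such an analysis would also contradict the trial's own sample-size basis, which allows for correlation within clusters.

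Separately, if a ward can be called a cluster, the random effect for the cluster does not say whether it has four levels or about 35. Two analysts following different sections could report different standard errors for the same hypothesis, and the choice would remain open after the data are seen.

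**Working it through.** The article prints no standard error or design effect, and Table 4 is an image that is not shown, so there is no figure of the plan's own to reproduce.

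**Inputs**
- ICC 0.03, two-sided 5% (Sample size).
- Four clusters and four starting dates (Randomisation).
- 3 to 12 months control, 3 months transition, 3 to 12 months intervention (Fig. 3 caption). I read this as even steps: control 3, 6, 9, 12 months and intervention 12, 9, 6, 3 months.
- Wards per cluster 6, 9, 13 and 8 (Table 2). These sum to 36, while the text says 35.
- Assumptions: respondent numbers (200, 500, 1000 per condition), how responses are spread, total variance scaled to 1, and a linear-model approximation.

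**Check 1: unadjusted regression on survey scores, responses proportional to exposure time**

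Shares of control data by cluster: 3/30, 6/30, 9/30, 12/30 = 0.1, 0.2, 0.3, 0.4. Shares of intervention data: 0.4, 0.3, 0.2, 0.1. The differences are 0.3, 0.1, -0.1, -0.3, with sum of squares S = 0.09 + 0.01 + 0.01 + 0.09 = 0.20.

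With n respondents per condition:
- True variance of the difference = 2(1 - 0.03)/n + S × 0.03 = 1.94/n + 0.006.
- Variance reported by ordinary regression ≈ 2/n.
- Type I error = 2[1 - Φ(1.96/r)], where r = √(true/reported).

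| n per condition | True | Reported | r | Type I error |
|---|---|---|---|---|
| 200 | 0.01570 | 0.0100 | 1.25 | 11.8% |
| 500 | 0.00988 | 0.0040 | 1.57 | 21.2% |
| 1000 | 0.00794 | 0.0020 | 1.99 | 32.5% |

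If each cluster is surveyed equally before and after, S = 0. The true variance is then 1.94/n against 2/n reported, r = √0.97 = 0.985, and type I error is 4.7% at every n.

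**Check 2: does the mixed model in Statistical methods have the same fault?**

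I used ward-by-quarter cells over six 3-month periods, with period effects included and a constant correlation of 0.03 placed either wholly at the randomised cluster or wholly at the ward. The cluster intercept is approximated as fixed. Entries are the ratio of true to reported standard error, with type I error in brackets.

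| Records per ward-quarter | Ordinary regression, all at cluster | Ordinary regression, all at ward | Cluster intercept, all at cluster | Cluster intercept, all at ward |
|---|---|---|---|---|
| 2 | 1.29 (13%) | 1.03 (5.7%) | 1.00 (5.0%) | 0.99 (4.7%) |
| 10 | 2.11 (35%) | 1.20 (10%) | 1.00 (5.0%) | 0.99 (4.7%) |
| 30 | 3.37 (56%) | 1.54 (20%) | 1.00 (5.0%) | 0.99 (4.7%) |
| 300 | 10.2 (85%) | 3.88 (61%) | 1.00 (5.0%) | 0.99 (4.7%) |

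The last row is near the scale of all admissions (48,609 / 4 / 36 ≈ 338 per ward-quarter). It shows what a literal, unclustered GLM could do for the record-based outcomes of H1 to H3.

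Ward intercepts with a constant cluster effect also give a ratio of 1.00, because every ward contributes to both conditions and the constant effect cancels.

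**The case against.** The strongest reply is that Statistical methods governs and Table 3 only summarises outcomes, sources and time points. Statistical methods opens with survey and health record data, calls for a mixed model with links suited to each outcome, and names binary and count outcomes. GLM in the table may simply stand for GLMM. Much of this stands. It is why a reader who infers that standard errors for H1 to H5 will be wrong goes too far: with period effects added, the stated mixed model is about right for a constant cluster or ward effect (Check 2). The reply does not remove the conflict for the continuous H4 and H5 scores, where only Table 3 names a model.

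Three further inferences are tempting but not supported:

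- **The Table 3 footnote.** ANOVA and chi-square for cluster comparisons belong to the descriptive approach marked by the asterisk. They describe how clusters differ and are not the test of the intervention.
- **A single random intercept is inadequate, or large-sample tests will be used.** A cluster intercept alone does understate the error if correlation drifts over time, but the article gives no autocorrelation. Nor does it say that z tests will be used. The cluster-by-period term and the degrees-of-freedom method may sit in an analysis plan that is not shown.
- **Wards will be analysed as if randomised.** The ward wording is one parenthesis against several statements of four clusters, and under constant effects either reading gives about the right standard error.

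The survey figures also depend on an unknown. Equal sampling before and after in each cluster brings unadjusted regression back to about 5%.

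**Conclusion.** The point holds as a contradiction within the article, not as proof that the final inference will fail. Table 3's entries for Outcomes 7 to 11 name no cluster term, which conflicts with Statistical methods and with the ICC behind the sample size. The entries for Outcomes 1 to 6 share the fault only if GLM is meant literally.

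Following Table 3, type I error for the survey scores would be about 12% to 33% at 200 to 1000 respondents per condition if responses track exposure time, and about 5% if each cluster is surveyed equally before and after. These figures rest on the article's ICC of 0.03, an even 3/6/9/12-month split, and assumed respondent numbers.

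The double use of the word cluster leaves the level of the random effect open (4 or about 35 units). That is an ambiguity to close, with no demonstrated error attached. Severity: should-fix.

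**What to change.** 1. In the Phase 3 Study design section, define the randomised cluster as one of the four hospital groups and delete the parenthesis that equates a ward with a cluster.
2. In Table 3, change the quantitative entries for Outcomes 1 to 11 to a mixed model with period fixed effects and a random effect for the randomised cluster, with wards nested within it. Leave the content analysis of complaints in Outcome 8 as it is.
3. In Statistical methods, add a sentence for continuous scores (linear mixed model) and name the levels of the random effects.
4. In the statistical analysis plan, consider a cluster-by-period term and small-sample degrees of freedom suited to four clusters. This is a recommendation and does not imply an error in the article.

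Cost: changes of wording on the same data, before the recruitment start stated as July 2026. The statistical price is wider intervals and some loss of nominal power compared with unclustered analyses. The size of that loss cannot be computed from the article, because Table 4 is not shown.
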